#### Analysis

Moderation will be evaluated by including an interaction term between the treatment variable and possible moderating variables in the outcome mixed effects regression models used in Aim 1. A significant interaction effect will conclude that the considered variable moderates the effect of PATHWEIGH on the outcome. Mediation analysis will be conducted using the multi-level modeling framework to account for clustering within clinics and providers [45, 46]. Clinic- and provider-level mediators will be restricted to those that can be collected from EMR in both the control and intervention phases. Specifically, we will fit two models: (1) a mediator model to describe the effect of the treatment on the mediator, and (2) an outcomes model to describe the effect of the mediator on the outcome, adjusting for the treatment. Additionally, to be considered a mediator, change in the mediator variable must occur prior to or during the period of patient-level change. Both models will be adjusted for relevant patient-, provider-, and clinic-level variables. The outcomes model will additionally adjust for a time effect to account for temporal effects in the stepped wedge design. These models will be adjusted to include the appropriate random effects and variables based on the level of the considered mediator variable (i.e., patient, provider, clinic). The mediation effect will be summarized as the product of the treatment coefficient from the mediator model and the mediator coefficient from the outcomes model. We will test the null hypothesis that this product is equal to zero, and a statistically significant result will indicate that there is strong evidence that the effect of the treatment on the outcome is mediated by the considered variable. If necessary, we will explore more complex multi-level structural equation models [47].

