For the primary analysis, although the parameter of interest is weight change at 6 months, weight collected from baseline to approximately 9 months post-baseline for the individual patient will be included in the primary analysis because patients may not have visits with recorded weight within the 6-month time frame. The mixed model will include random intercepts for patient, provider, and clinic, along with fixed effects for time and intervention condition. The time effects are two-fold: (i) calendar time, divided into four 1-year periods and included as a categorical variable to flexibly model its effect on the outcome and account for temporal trends, and (ii) individual patient time, included as a continuous variable (i.e., time from baseline) to accommodate varying visit times determined by each patient’s visit schedule. The intervention condition variable will be a binary indicator that is equal to zero if the patient’s index visit occurs at a clinic when it is in the control condition and becomes equal to 1 when the patient has an index visit at a clinic after it has crossed into the intervention condition. Patient-, provider-, and practice-level covariates will be included in models if deemed to be potential confounders in univariate models. An additional fixed effect for the interaction between patient time and intervention condition will be used to estimate the parameters of primary interest, i.e., the difference in change in outcomes over time between the intervention and control conditions. The primary analysis will test the null hypothesis that the interaction effect coefficient is equal to zero to determine whether there is a significant difference in weight change between the PATHWEIGH and SOC conditions. Using the model, we will report the mean weight change in the control and intervention groups and their difference at 6 months, with corresponding 95% confidence intervals and *p* values.

To examine the secondary binary outcomes of weight maintenance (defined as < 10% weight gain at 12 and 18 months), we will use generalized linear mixed models. Since this analysis will involve a single outcome per patient, the model will only include a random intercept for provider and clinic. The test of intervention effectiveness will be captured by the fixed effect term for the intervention condition.

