### Aim 2: Identify patient, provider, and clinic-level predictors that are associated with weight loss and weight loss maintenance

#### Outcomes and measures

Patient-level predictors will be captured from the EMR for each visit. Potential patient-level moderators will include age, sex, race/ethnicity, insurance status, baseline BMI, baseline use of medication that may contribute to weight gain, and score > 9 on Patient Health Questionnaire-8 or -9 (PHQ8, PHQ9), or Generalized Anxiety Disorder-7 (GAD7). Patient-level mediators will include treatment prescribed, in particular prescription of anti-obesity medication and performance of an endoscopic or surgical procedure with bariatrics. Provider-level predictors that can be obtained from EMR include provider age, sex, years in practice, and percent time performing clinical duties. Practice-level predictors include patient and provider number and demographics for each, as well as payor mix.

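### In the 6-month weight model, the stated moderation test (treatment × moderator) does not test whether PATHWEIGH's effect on weight loss differs between patient groups

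*Protocol article*

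**What the plan says.** The Aim 1 Analysis section of the protocol article defines the weight model. The response is weight measured repeatedly, baseline included: "weight collected from baseline to approximately 9 months post-baseline for the individual patient will be included in the primary analysis". The structure is given as "The mixed model will include random intercepts for patient, provider, and clinic, along with fixed effects for time and intervention condition". Treatment is a 0/1 variable fixed at the index visit: "The intervention condition variable will be a binary indicator that is equal to zero if the patient’s index visit occurs at a clinic when" the clinic is still in the control condition, and one after crossover. The effect of interest is carried by a further term: "An additional fixed effect for the interaction between patient time and intervention condition will be used to estimate the parameters of primary interest". The primary hypothesis is about that term: "The primary analysis will test the null hypothesis that the interaction effect coefficient is equal to zero".

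The same section gives separate mixed models for binary weight-loss maintenance at 12 and 18 months. These have one outcome per patient, and the treatment effect is the main effect of condition.

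Aim 2 is to "Identify patient, provider, and clinic-level predictors that are associated with weight loss and weight loss maintenance". Its Analysis section returns to the Aim 1 models: "Moderation will be evaluated by including an interaction term between the treatment variable and possible moderating variables in the outcome mixed effects regression models". The decision rule follows: "A significant interaction effect will conclude that the considered variable moderates the effect of PATHWEIGH on the outcome". Neither sentence mentions patient time.

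**The concern.** The Aim 2 rule adds one kind of term to two kinds of model. In the binary maintenance models the treatment effect is the condition coefficient, so condition × moderator is the right test. In the weight model the condition coefficient is the between-condition difference in weight at patient time zero, and the effect on weight change is condition × patient time. Crossing the 0/1 indicator with sex, insurance or baseline BMI therefore asks whether the two conditions differ in weight level by different amounts across those groups. It does not ask whether PATHWEIGH produces more weight loss in one group than in another.

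At stake is the moderator half of a stated specific aim, for the 6-month weight outcome. A rule that declares moderation from this coefficient can miss real moderators of weight loss. It can also name moderators where there are none.

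**Working it through.** **1. The plan's own figures.** The Sample size section gives detectable standardized effects of 0.118 (ICC 0.02) and 0.121 (ICC 0.05). The Hussey–Hughes variance with 57 clinics (20/18/19), four periods and 30 patients per clinic-period gives 0.1170 and 0.1201, within 1%. The conversions also hold: 0.118 × 10.7 = 1.26 kg and 0.121 × 10.7 = 1.29 kg. These figures concern the overall treatment effect. The article states none for moderation, so the point rests on model structure.

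**2. The model as written.** Let t be patient time in months, G condition and M a binary moderator. Leave out random effects and calendar period:

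E[weight] = b0 + b1·t + b2·G + b3·G·t + b4·M + b5·G·M

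- Change from 0 to 6 months: 6·b1 + 6·b3·G.
- Treatment difference in that change: 6·b3, whatever the value of M.
- b5, the tested coefficient, does not multiply t. It is a shift in weight that is constant over follow-up and already present at t = 0.

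Moderation of weight loss needs b7·G·M·t. The treatment difference in 6-month change is then 6·b3 when M = 0 and 6·(b3 + b7) when M = 1.

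**3. Dilution of a real effect.** With the three-way term left out, part of a true slope difference leaks into b5, roughly the slope difference times the mean patient time of the recorded weights. One simulation used a weight at month 0 and three more spread over months 0.5 to 9. Mean patient time is then 3 × 4.75 / 4 = 3.56 months, so the expected share of the 6-month difference is 3.56 / 6 = 0.59. Simulated shares are:
- 0.66 / 1.26 = 0.52
- 0.73 / 1.26 = 0.58
- 1.53 / 2.52 = 0.61
- 1.21 / 2 = 0.605 (a separate simulation)

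The share is about a half or slightly more, and it depends on the visit pattern.

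**4. Hand check of power for a 2 kg moderation.** Take 6840 patients in four equal condition-by-moderator cells of 1710, ignoring clustering and calendar time; √(4/1710) = 0.0484.
- Three-way term, change SD 10.7 kg (Sample size section): SE = 10.7 × 0.0484 = 0.52 kg; 2 / 0.52 = 3.86; power about 97%.
- Two-way term, assumed baseline SD 20 kg: SE ≈ 20 × 0.0484 = 0.97 kg; half of 2 kg is 1 kg; 1 / 0.97 = 1.03; power about 18%.
- Two-way term, assumed baseline SD 10 kg: SE ≈ 0.48 kg; 1 / 0.48 = 2.07; power about 54%.

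**5. Simulation, 6840 patients, baseline SDs assumed.**

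| Scenario | Two-way rejects | Three-way rejects |
|---|---|---|
| True 2 kg moderation of loss, change SD about 10.6 kg, baseline SD 20 / 10 kg | about 15% / 48% | 97–98% |
| True 2 kg, separate simulation, baseline SD 20 kg | 25% | about 98% |
| True 1.26 kg, residual SD 5 kg, patient SD 20 / 10 kg | 11% / 33% | 99–100% |
| No moderation of loss; 3 kg starting-weight difference that depends on the moderator, SD 20 to 10 kg | 91–100% | 6–7% |
| Same 3 kg scenario, separate simulation, SD 20 kg | about 80% | not reported |
| No moderation of loss; 4 kg such difference, SD 20 kg | 98% | 6% |
| Neither | 5% | 6% |

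The 99–100% for 1.26 kg is optimistic because the residual SD of 5 kg is assumed. The three-way figure of about 97% for 2 kg agrees with the hand check from the article's own change SD.

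**The case against.** The best defence is that the Aim 2 sentence is generic. It covers several models at once and speaks of the treatment variable where Aim 1 speaks of the intervention condition variable. It also aims at moderation of PATHWEIGH's effect, which Aim 1 defines for weight as a difference in change over time. Read generously, moderating that effect means crossing the moderator with the time × condition term. An article may also leave the full list of model terms to the analysis plan. This has some force: the authors plainly know where their effect lies, and the intended test may be the right one. But the article does not leave the matter open. It names the term and the decision rule, while Aim 1 makes the treatment variable a 0/1 indicator and introduces the time interaction as an additional term. An analyst who follows the text fits the wrong model.

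A reader might infer more than the documents support:

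- **That PATHWEIGH merely attracting heavier or lighter patients would create false moderators.** A starting-weight shift common to all patients is absorbed by the condition main effect. The shift must itself vary by moderator level.
- **That the protocol expects such a shift.** The Aim 1 Analysis section allows that patients in the two conditions may differ through selection. It names neither starting weight nor a difference that varies by moderator.
- **That the two-way test is blind to weight loss.** It picks up about half of a true difference.
- **That all moderation analyses in Aim 2 are affected.** The binary maintenance models are not.

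The magnitudes also depend on assumed baseline SDs and visit patterns. The change-SD-10.6 and residual-SD-5 simulations omit clinic, provider and calendar effects.

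**Conclusion.** The point holds for the longitudinal 6-month weight model only. The algebra needs no assumed figure: with only the two-way term, the effect on 6-month change is constrained to be equal across moderator levels, and the tested coefficient is mainly a baseline difference in level.

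The size is illustrative. For a 2 kg moderation and baseline SDs of 20 to 10 kg, power is about 15 to 50% for the two-way term against about 97% for the three-way term. The false-positive risk is conditional: it arises only if the between-condition difference in starting weight varies by moderator level, and the documents give no figure for how likely that is.

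The primary Aim 1 test, the maintenance comparisons and the sample size are unaffected. The correction should be made, but it does not threaten the trial's main conclusion.

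**What to change.** State in the analysis plan that, for the 6-month weight outcome, moderation is tested by treatment × moderator × patient time, with all lower-order terms in the model (moderator × patient time and treatment × moderator included). Report the treatment effect on 6-month weight change at each moderator level with a 95% confidence interval. State that treatment × moderator remains the test for the binary 12- and 18-month maintenance models.

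A moderator × period × patient time term is not needed: the Aim 1 model has no period × patient time term for it to extend.

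The cost is a sentence or two, with no new data and no change to the design or to the primary analysis.

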## Aims and hypotheses

The specific aims of the current research are to:
Compare the effectiveness of PATHWEIGH versus standard of care (SOC) on weight loss and weight loss maintenance.Identify patient, provider, and clinic-level predictors that are associated with weight loss and weight loss maintenance.Describe factors associated with practice adoption, implementation, and maintenance of PATHWEIGH.

We hypothesize that PATHWEIGH will lead to greater weight loss at 6 months (primary) and greater weight loss maintenance at 12 and 18 months (secondary) compared to SOC [Hypothesis I]. Key patient, clinician, and clinic characteristics will mediate and moderate patient weight loss and weight loss maintenance [Hypothesis II]. Effective implementation will be vital to anticipated implementation and clinical outcomes [Hypothesis III].

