### Sample size

A conservative sample size estimate is 6840 total patients (120 patients per clinic from 57 clinics) that assume a minimum of 30 eligible patients per clinic per year based on the smallest clinic. We present the power calculations assuming an intraclass correlation coefficient (ICC) between 0.02 and 0.05. With this design, we will have 80% power (alpha=0.05, two-sided) to detect a standardized effect size of 0.118 (ICC=0.02) to 0.121 (ICC=0.05). For our primary effectiveness outcomes, we estimate a standard deviation (SD) of 10.1 percentage points for percentage change in weight using our pilot study, and a similar SD estimate of 10.7 for absolute (kg) change in weight. Thus, with 80% power we can detect a mean difference in weight change of 1.19 (ICC=0.02) to 1.22 (ICC=0.05) percentage points between the control and intervention conditions, and a mean difference in absolute weight change of 1.26 kg (ICC=0.02) to 1.29 kg (ICC=0.05).

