#### Staff workflow

Placards may be placed at the front desk of the clinics alerting patients that they may make a weight-prioritized visit if they would like medical assistance with their weight. Each clinic or provider will determine the number of weight-prioritized visits available. Once a patient schedules a weight-prioritized visit, Epic will request they complete a specified weight management questionnaire upon e-check-in prior to their visit. Medical assistants (MAs) will review provider schedules ahead of time to ensure patients complete this questionnaire prior to their visit. At the time of the patient visit, MAs will record the patient’s weight and vital signs with no other assistance required. Collectively, the workflow maximizes time for the clinician-patient conversation in the context of the Patient-Centered Medical Home [10].

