#### Clinician workflow

To optimize efficiency and guide care, health care providers are encouraged to use the PATHWEIGH weight management SmartSet in Epic. A SmartSet is a documentation template used in the ambulatory setting comprised of a group of orders and other elements, such as notes, chief complaints, medications, and levels of service charges, that are commonly used together to document a specific type of visit. This SmartSet addresses the following.
Diagnosing overweight or obese patients with a BMI > 25 kg/m^2^ or > 30 kg/m^2^, respectively, recognizing these as bona fide disease states [6]Linking diagnoses for weight-related comorbidities to facilitate reimbursementPre-populating information from the patient weight management questionnaire to serve as documentation and to guide the clinician-patient discussion, and flagging weight management strategies based on guidelines from the Obesity Society [32], specifically, the discussion of lifestyle change for patients with BMI ≥ 25 kg/m^2^, consideration of medications impacting obesity as well as anti-obesity medication at BMI ≥ 30 kg/m^2^ (or BMI ≥ 27 kg/m^2^ with weight-related comorbidities) and consideration of bariatric surgery for BMI ≥ 40 kg/m^2^ (or BMI ≥35 kg/m^2^ with weight-related comorbidities)Providing options for orders that include laboratory testing, referrals, or procedures

Behavioral health professionals work alongside many of the primary care providers and are encouraged adjuncts to facilitate weight loss. Use of the PATHWEIGH tools is entirely optional for clinicians. Use may be deployed by the clinicians in advance of the visit or if they or the patient spontaneously decides to prioritize weight management. The process strongly encourages regular follow-up (usually at 4–6 week intervals and more often initially). A key advantage is that the clinician is the patient’s regular provider and will have an ongoing relationship with the patient over time and can safely manage or discontinue medications or other issues for weight-related comorbidities.

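### Clinic- and provider-level moderators are tested in models with random intercepts only, so the interaction is judged against patient-level error and false moderators may be declared too often

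*Protocol article*

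**What the plan says.** Protocol article, Aims and hypotheses (Hypothesis II): "Key patient, clinician, and clinic characteristics will mediate and moderate patient weight loss and weight loss maintenance". The Abstract (Methods) likewise says that predictors at patient, provider and clinic level will be found by mediator and moderator analyses.

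Aim 2, Outcomes and measures, uses the word moderators for patient variables only. Provider and practice variables are called predictors: "Practice-level predictors include patient and provider number and demographics for each, as well as payor mix".

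Aim 2, Analysis, tests moderation by "including an interaction term between the treatment variable and possible moderating variables in the outcome mixed effects regression models used in Aim 1". It adds that a significant interaction will be taken to show that the variable moderates the effect.

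Aim 1, Analysis, defines those models. The weight model has random intercepts for patient, provider and clinic, and its treatment effect is the interaction of patient time with intervention. The binary maintenance model has random intercepts for provider and clinic. Neither has a random intervention effect or a random time slope at clinic or provider level. The sentence in Aim 2, Analysis, about matching random effects to the level of the variable refers to mediators.

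Two statements bear on whether effects may differ between clinics: "Use of the PATHWEIGH tools is entirely optional for clinicians" (Clinician workflow) and "Each clinic or provider will determine the number of weight-prioritized visits available" (Staff workflow).

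**The concern.** Payor mix or clinic size takes one value per clinic. Its interaction with PATHWEIGH asks whether clinics with different values have different effects, so the replicates are the 57 clinics (or the providers, for a provider characteristic). If effects differ between clinics for unrelated reasons, that scatter belongs in the standard error of the interaction. A model with random intercepts only has no place for it. Its standard error keeps shrinking as patients accrue, while the true one is bounded by the number of clinics.

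The weight model has a further gap. Its effect is a difference in slopes over patient time, and random intercepts largely cancel from within-patient change. Ordinary clinic-to-clinic differences in average weight change are then also treated as independent patient noise, even if the PATHWEIGH effect is the same everywhere.

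Aim 2 is a specific aim and is meant to guide which practices benefit. With significance as the stated rule, a spurious clinic moderator would become a finding.

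**Working it through.** **Inputs from the protocol.** 57 clinics in sequences of 20, 18 and 19 (Table 1); three steps and four 1-year periods (Design and randomization; Aim 1, Analysis); "a minimum of 30 eligible patients per clinic per year based on the smallest clinic"; ICC 0.02 to 0.05; SD of weight change 10.7 kg (Sample size).

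**Assumed, not in the protocol.** Between-clinic SD of the true PATHWEIGH effect, ω, of 0.06 to 0.12 outcome SD. This is half to all of the detectable effect of about 0.12, or 0.06 × 10.7 = 0.64 kg to 0.12 × 10.7 = 1.28 kg. Also 100 or 300 patients per clinic-year. Nearly 500,000 patients over 57 clinics is about 8,800 each, so 100 to 300 is roughly 1 to 3% of a clinic's patients.

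**Step 1: the plan's own figure.** The plan uses "6840 total patients (120 patients per clinic from 57 clinics" and says "we will have 80% power (alpha=0.05, two-sided) to detect a standardized effect size of 0.118 (ICC=0.02) to 0.121 (ICC=0.05". Hussey-Hughes variance with fixed periods, a random clinic intercept, total SD 1 and 30 per clinic-year gives SE 0.0418 (ICC 0.02) and 0.0429 (ICC 0.05). The detectable effect is (1.960 + 0.842) × SE = 0.117 and 0.120, against the stated 0.118 and 0.121. The figure reproduces. The calculation has one ICC and no between-clinic variation in effect.

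**Step 2: clinic-intercept model of change.** For clinic *i*, take the four period means with design matrix D (periods, treatment x, moderator M, x·M), where M is standard normal with no true effect.
- Fitted covariance: V = [(1 − ρ)/m]·I + ρ·J.
- True covariance: V* = V + ω²·x·xᵀ.
- Model variance: A⁻¹, with A = Σ DᵀV⁻¹D.
- True variance: A⁻¹BA⁻¹, with B = Σ DᵀV⁻¹V*V⁻¹D.
- With r = true SE / model SE for the x·M coefficient, the rejection rate is 2Φ(−1.96/r).

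| Patients per clinic-year | ω = 0 | ω = 0.06 | ω = 0.12 |
|---|---|---|---|
| 30 (stated minimum) | 5% | r 1.05, 6% | r 1.18, 10% |
| 100 (assumed) | 5% | r 1.15, 9% | r 1.51, 19% |
| 300 (assumed) | 5% | r 1.39, 16% | r 2.18, 37% |

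Results for ICC 0.02 and 0.05 are nearly identical. A simulation with a binary outcome, a linear clinic-intercept model and 1,500 runs per cell gave 5.9 and 9.9% at 30, 7.7 and 21.7% at 100, and 15.7 and 37.8% at 300. Its cells without heterogeneity gave 5.0, 5.1 and 6.5%.

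**Step 3: longitudinal weight model.** Take two visits per patient, and assume the term meant is moderator × intervention × patient time (a two-way moderator × intervention term would test weight level, not change). Intercepts cancel from the within-patient change, so the fitted covariance of the period means is I/m. The true one is [(1 − ρ)/m]·I + ρ·J, with ρ the protocol's ICC applied to weight change and ω = 0.

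| Patients per clinic-year | ρ = 0 | ρ = 0.02 | ρ = 0.05 |
|---|---|---|---|
| 30 | 5% | r 1.17, 9% | r 1.39, 16% |
| 100 | 5% | r 1.51, 20% | r 2.05, 34% |

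A separate calculation gave about 10 to 17% and 20 to 35%. A binary moderator held by 8 of 57 clinics (the rural count) gives nearly the same rates.

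**Step 4: does the repair work?** This was checked by simulation only in the clinic-intercept model of change: 100 per clinic-year, ICC 0.02, 250 runs per setting, so the Monte Carlo SE at 5% is √(0.05 × 0.95/250) = 1.4 points. With effect SDs of 1 and 2 kg, intercepts only rejected in 18% and 26% of runs. Adding a clinic random intervention effect with t on 55 df gave 6.0% and 5.6%. With no heterogeneity the rates were 4.8% and 1.2%, so the repaired test can be conservative.

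**The case against.** The best defence has four parts.

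- **Scope.** Only patient variables are listed as moderators; clinic and provider moderation is read from Hypothesis II and the Abstract. This narrows the point but does not remove it, because both places announce moderation at those levels and only one method is given.
- **Detail left to the analysis plan.** Degrees of freedom and level-specific random slopes for a secondary aim often sit there, and the weight model's description does not say that intercepts are the only random effects. That is fair as to the degrees of freedom. But the moderation text points to models whose random effects are named, attaches a decision rule, and provides for level-matched random effects for mediators alone.
- **Evidence of heterogeneity.** Optional use governs uptake and visit supply governs who enters; neither shows that effects differ. This stands: they make variation plausible and do not measure it. An ω of 0.12 is large, since with a mean effect of 0.12 about 16% of clinics would do worse under PATHWEIGH.
- **Simulation quality.** The binary-outcome simulation used a linear model with a clinic intercept only, and its 6.5% at 300 with no heterogeneity is about 2.7 Monte Carlo SEs above 5%. That is why the conclusion rests on the closed-form rates.

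A reader might infer that false moderators will be declared, or that any single clinic-level test runs well above 5%. The documents do not support either. At 30 per clinic-year and the smallest assumed SD, the clinic-intercept model gives about 6%, and with no between-clinic variation the rate is nominal.

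**Conclusion.** The point holds as a raised risk of false positives for clinic- and provider-level moderators, not as a certainty. In a clinic-intercept model of change, the rate for one irrelevant clinic moderator is about 6 to 10% at the stated minimum of 30 per clinic-year, 9 to 20% at 100 and 16 to 37% at 300, given an assumed effect SD of 0.06 to 0.12. In the weight model it is about 9 to 17% at 30 and 20 to 35% at 100 with no effect heterogeneity, if the protocol's ICC applies to weight change. If neither effect nor slope varies between clinics, it is 5%.

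Provider-level moderators share the structure, with about 400 clinician full-time equivalents as units, but were not computed. Patient-level moderators are little affected. The point concerns Aim 2; the primary hypothesis test was not assessed here. It should be corrected because the rule is explicit and the repair is short.

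**What to change.** In Aim 2, Analysis, state the random effects for moderation by level:

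- **Clinic-level moderators, weight model:** add a clinic random patient-time slope and a clinic random intervention-by-patient-time effect. A clinic random intervention effect alone does not supply the missing slope variation.
- **Clinic-level moderators, binary maintenance model:** add a clinic random intervention effect.
- **Provider-level moderators:** add the matching provider terms.
- **Test:** use degrees of freedom based on the number of clinics (57 − 2 = 55, approximately) or providers, or clinic-clustered robust variance with a small-sample correction.

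The same passage should say that for weight change the moderator term is the three-way interaction with patient time, if that is intended.

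The cost is a sentence or two of analysis wording and no extra data. Intervals widen and power falls for these moderators, reflecting the 57 clinics available, and the test is somewhat conservative if there is no heterogeneity.

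### Aim 2 makes every significant interaction a conclusion of moderation, over at least 21 likely tests, with no ranking, exploratory label or error control stated in the protocol

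*Protocol article*

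**What the plan says.** Moderation is part of a formal hypothesis of the trial (Aims and hypotheses): "Key patient, clinician, and clinic characteristics will mediate and moderate patient weight loss and weight loss maintenance [Hypothesis II".

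The candidates are listed under Aim 2, Outcomes and measures. The word *moderators* is attached to patient-level variables only: "Potential patient-level moderators will include age, sex, race/ethnicity, insurance status, baseline BMI, baseline use of medication that may contribute to weight gain", followed by "score > 9 on Patient Health Questionnaire-8 or -9 (PHQ8, PHQ9), or Generalized Anxiety Disorder-7 (GAD7". That makes 7 or 8 variables, depending on whether the depression and anxiety scores are combined. The provider- and practice-level variables are called predictors: "Provider-level predictors that can be obtained from EMR include provider age, sex, years in practice, and percent time performing clinical duties", then patient and provider numbers, demographics of each, and payor mix. The Methods part of the Abstract says that predictors at all three levels will be identified by mediator and moderator analyses.

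Under Aim 2, Analysis, interaction terms are tested "in the outcome mixed effects regression models used in Aim 1". Those models cover weight to 6 months and weight loss maintenance at 12 and at 18 months. The reading of the test is then fixed: "A significant interaction effect will conclude that the considered variable moderates the effect of PATHWEIGH on the outcome". The mediation part of the same section says that a statistically significant product of coefficients indicates strong evidence of mediation.

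**The concern.** The quoted sentence is a decision rule for each variable: one significant interaction yields one stated conclusion. It is to be applied to a list of candidates and to several outcomes. No moderator is singled out as the key one, and the moderator tests are not described as exploratory or hypothesis-generating. The only exploratory wording in that section concerns more complex structural equation models.

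Followed as written, the rule would report some chance interactions as established effect modifiers. The candidates include sex, race/ethnicity and insurance status, where a false statement about who benefits would be hard to withdraw. The mediation sentence invites the same kind of over-reading.

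**Working it through.** **1. The plan's own power figure.** The article gives one: "With this design, we will have 80% power (alpha=0.05, two-sided) to detect a standardized effect size of 0.118 (ICC=0.02) to 0.121 (ICC=0.05". Inputs from Sample size and Design and randomization are 57 clinics in sequences of 20, 18 and 19, four one-year periods, and 30 patients per clinic-year (57 × 120 = 6840). The Hussey-Hughes variance for total SD 1, with σ² = (1 − ICC)/30 and τ² = ICC, is

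Var = Iσ²(σ² + Tτ²) / [(IU − W)σ² + (U² + ITU − TW − IV)τ²].

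- I = 57 and T = 4.
- U = 20·3 + 18·2 + 19·1 = 115.
- W = 20² + 38² + 57² = 5093.
- V = 20·9 + 18·4 + 19·1 = 271.
- IU − W = 1462, and U² + ITU − TW − IV = 3626.

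ICC 0.02: Var = 0.2098/120.28 = 0.001744, SE 0.0418, detectable effect 2.80 × SE = 0.117 (stated 0.118).

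ICC 0.05: Var = 0.4182/227.60 = 0.001837, SE 0.0429, detectable effect 0.120 (stated 0.121).

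Power at the stated effects is 80.7% and 80.6%, so the figure is reproduced. It concerns the main effect only. The article gives no power or error rate for Aim 2.

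**2. Number of tests.**

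- Named moderators: 6 + 1 or 2 = 7 or 8. Over three outcomes this is 21 or 24 tests.
- Wider reading: add 4 provider-level and at least 5 practice-level predictors, giving 16 or 17 candidates. Over three outcomes this is 48 or 51 tests.

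Each variable is counted as one test per outcome.

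**3. Chance of at least one false conclusion.** Two assumptions are needed: 0.05 per test (the article states this level only for the sample size) and no true moderation. For n independent tests the chance is 1 − 0.95ⁿ, and the expected number of false conclusions is 0.05n.

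| Moderators × outcomes | Tests | Chance of ≥ 1 | Expected number |
|---|---|---|---|
| 7 × 1 | 7 | 0.302 | 0.35 |
| 8 × 1 | 8 | 0.337 | 0.40 |
| 7 × 3 | 21 | 0.659 | 1.05 |
| 8 × 3 | 24 | 0.708 | 1.20 |
| 16 × 3 | 48 | 0.915 | 2.40 |
| 17 × 3 | 51 | 0.927 | 2.55 |

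**4. Allowing for correlation.** The document gives no correlations, so these are assumed. Normal test statistics were simulated (200,000 draws, two-sided 0.05), with the correlation for a different moderator and a different outcome set to the product of the two.

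| Between moderators | Between outcomes | 21 tests | 48 tests |
|---|---|---|---|
| 0 | 0.5 | 0.61 | 0.88 |
| 0.2 | 0.5 | 0.59 | 0.85 |
| 0 | 0.8 | 0.51 | 0.81 |
| 0.3 | 0.8 | 0.47 | 0.73 |
| 0.5 | 0.8 | 0.40 | 0.61 |

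Correlation lowers the chance of at least one false conclusion. It does not change the expected number, which is a sum of the separate error rates.

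**5. Scope of a correction.** Under the same null with independent tests, Benjamini-Hochberg at 5% holds the chance of any false conclusion at 5% over the family to which it is applied. Applied separately to each of three independent outcomes, it leaves 1 − 0.95³ = 14% overall. Applied to all tests together, it leaves 5%. For comparison, Bonferroni over 48 tests uses 0.05/48 = 0.00104 per test and gives 0.049.

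**The case against.** The strongest defence is that *significant* is not defined for Aim 2. The sentence may do no more than say what an interaction means, and it would fit an adjusted threshold as well as a nominal one. This is a condensed article, the statistical analysis plan is not shown, and multiplicity for secondary moderator tests is often settled there. This part stands. A reader might infer that the tests will be unadjusted, but the article does not say so, and its silence on adjustment is not by itself an error. What remains is the wording that is present: significance is equated with a conclusion, for an unranked list under a formal hypothesis.

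A reader might also infer that 16 or more moderators will be tested and that a false finding is therefore very likely, at about 91%. The document does not establish this. Only 7 to 8 variables are named as moderators. The Abstract and Hypothesis II support moderation at all three levels, but nowhere is it said that each provider- and practice-level predictor is tested as a moderator on every outcome. The 91% also needs 48 tests that are all independent and all null. Independence is implausible: the two maintenance outcomes share the 6-month weight as reference, and provider age overlaps with years in practice.

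The article does call the moderators *potential* and *possible*. Those words describe their status before the test, not the conclusion drawn after it. It is also fair that no section uses a moderator result to restrict or target PATHWEIGH, so downstream harm is a risk and not a stated plan. For the 6-month outcome alone, the 7 named moderators give 30%.

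**Conclusion.** The point holds in limited form. The inferential wording for moderators, and the parallel wording for mediators, is stronger than the described testing can support. It is neither qualified as exploratory nor tied to any error control in this document.

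On the named moderators over three outcomes, the chance of at least one false conclusion is 66% to 71% if the tests are independent, and about 40% to 61% for 21 tests under the assumed correlations. The expected number of false moderators is 1.05 to 1.2. On the wider reading of about 48 tests, the range is about 61% to 92%, with 2.4 expected.

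All these figures assume 0.05 per test, no true moderation and testing on all three outcomes. An adjustment set elsewhere would reduce them. No figure is given for the mediators, because the clinic- and provider-level candidates are not enumerated. The test of the primary hypothesis and the sample size are not affected.

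**What to change.** Replace the interaction sentence under Aim 2, Analysis with text to this effect: interaction estimates with 95% confidence intervals will be reported for every listed moderator and every outcome; a nominally significant interaction will be reported as hypothesis-generating; moderation will be concluded only for interactions that survive a pre-stated multiplicity procedure applied across all moderators and outcomes together. Benjamini-Hochberg over the whole family is one option. The choice of procedure is open to debate, but its family should match the set of tests on which conclusions are drawn. The text should also say which provider- and practice-level predictors are to be tested as moderators, so that the family can be counted.

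Soften the mediation sentence in the same way, so that a significant product is reported as consistent with mediation unless it survives the stated procedure.

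The cost is a few sentences and less power to declare an individual moderator. Data collection does not change.
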